## 3. STUDY DESIGN

This study is a randomized, placebo-controlled, crossover study with 20 type II diabetic patients (both men and women). Subjects will be recruited in and near the vicinity of Maastricht by means of posters distributed in university and hospital buildings, advertisements in local newspapers, the hospital bulletin and on the internet ([www.digiprik.nl](http://www.digiprik.nl)). Subjects who have participated in earlier studies and indicated to be interested in participation in other studies will be contacted. Before screening, subjects will be informed about the procedures during the study via oral and written information (see information brochure). After information is given, subjects can consider participation for at least 3

days. When positive, informed consent will be obtained before start of the study. Participation will be on voluntary basis and people who are willing to participate will be invited for a screening visit. Subjects will be informed about their results obtained during the screening and advised to consult their general practitioner when values of the screening parameters are outside the normal ranges. Subjects have to state specifically on the informed consent page that they do not object to receiving data on accidental findings. When subjects fulfil all inclusion criteria, they may enter the study.

The intervention will consist of control capsules, vitamin E capsules with a daily intake of 900 mg, and lipoic acid capsules with a daily intake of 600 mg. These doses are based upon previous research showing reduced oxidative stress at these intakes (19,22). During the first 4 weeks of the study (period I), subjects will be provided with the control capsules, the vitamin E capsules or the lipoic acid capsules. After period I, the subjects will return to their normal pattern (indicating no vitamin supplementation) for 4 weeks (washout period). Then, the subjects will cross over to another dietary regime in period II. Hereafter they will again return to their normal eating habits for 4 weeks and cross over to the last dietary regime in period III. There will be no dietary restriction as long as dietary habits remain stable over the entire study. During the entire study period (including the washout periods), the subjects are not allowed to consume any dietary supplements other than those provided by us. All subjects must adhere to each dietary regime, meaning consumption of control capsules, vitamin E capsules and lipoic acid capsules during the three periods. Compliance can be monitored by measurement of serum vitamin E and lipoic acid concentrations.

As depicted in table 1 (Appendix 1), the subjects will come to the department at the beginning of period I, II and III (weeks 1, 9, and 17), after three weeks of each period (weeks 3, 11 and 19) and at the end of each period (weeks 4, 12 and 20). During these visits, a fasting blood sample will be taken and body weight is measured. Based on earlier studies we expect a washout period of 4 weeks to be long enough. All subjects will pick up their supply of products when they visit the department for the blood sampling at the beginning of period I, II and III. The capsules will be provided in bottles containing one-week portions of 23 capsules (3 capsules a day, and 2 extra capsules). Capsules that are left over at the end of the week must be returned to the department and will be counted. Capsules are similarly packed to assure blinding of the subjects and investigators. Moreover, the bottles will be color-coded to blind both the subjects and the investigators. The subjects will record in a diary the amounts and times of consumption of the capsules and they will also be asked to record every signs of illnesses, medication used and any deviations from protocol. Furthermore, they will be urged not to change their dietary habits, level of physical activity, use of alcohol or of oral contraceptives throughout the

study. A registered dietician will check these dairies at each visit. At the end of the three periods I, II and III, the subjects will also fill out a food frequency questionnaire to estimate their habitual intake over the previous 4 week period (weeks 4, 12, 20).

#### **4. STUDY POPULATION**

##### **4.1 Population**

Subjects will include 20 type II diabetic patients, aged between 18 and 75 years that have to fulfil the inclusion criteria as described below. From our previous experiences, we know that a high proportion of people of >75 years do have one or more of the exclusion criteria as formulated in paragraph 4.4. Because we do not want to encumber these subjects unnecessarily, we have decided to set the upper limit for age at 75 years.

##### **4.2 Screening visit**

The subjects will be invited for a screening visit, this visit will include recording of:

- body weight
- length
- blood pressure (diastolic and systolic)
- blood parameters (serum total cholesterol, triacylglycerol and glucose concentrations)
- use of medication
- current disease and history of coronary heart disease

Subjects will come to the department twice for two screening visits. During the first screening visit, the subjects will be weighed, blood pressure will determined in four-fold (the first measurement will be discarded and the last three measurement will be averaged), body height will determined and a venous blood sample (1\*3.5 ml, 1\*2 ml) will be drawn for analysis of serum total cholesterol, triacylglycerol, glucose concentrations and liver function markers.

During the second screening visit, body weight and blood pressure will be determined again and a second venous blood sample (1\*3.5 ml and 1\*2 ml) will be drawn for analysis of serum total cholesterol, triacylglycerol and glucose concentrations.

##### **4.3 Inclusion criteria**

The inclusion criteria are:

- aged between 18 and 75 years
- Body Mass Index (BMI) between 20-30 kg/m^2
- mean serum total cholesterol < 8.0 mmol/L

- mean serum triacylglycerol < 3.0 mmol/L
- diagnosed with diabetes mellitus type 2 on a clinical basis

#### 4.4 Exclusion criteria

The exclusion criteria are:

- unstable body weight (weight gain or loss > 3 kg in the past two months)
- active cardiovascular diseases like congestive heart failure or recent (<6 months) event (acute myocardial infarction, cerebral vascular incident)
- severe medical conditions that might interfere with the study such as epilepsy, asthma, chronic obstructive pulmonary disease, inflammatory bowel disease and rheumatoid arthritis
- use of medication such as corticosteroids, diuretics or lipid lowering therapy
- use of insulin therapy
- abuse of drugs or alcohol (>21 units per week)
- not willing to stop the consumption of dietary supplements 1 month before the start of the study (wash-in period)
- use of an investigational product within another biomedical study within the previous month
- pregnant or breast-feeding women
- current smoker

#### 4.5 Sample size calculation

In our previous study, we were able to detect a decrease of 0.07 ng/mL in 7b-OH-campesterol concentrations in healthy volunteers upon plant stanol consumption. A larger decrease in oxyphytosterol concentrations is expected upon vitamin E and lipoic acid consumption, as they are antioxidants and research has already shown that they are able to decrease oxidative stress markers. A recent study found a decrease of 28% in oxysterol concentrations upon vitamin E consumption [18]. We would expect larger decreases upon vitamin E and lipoic acid consumption in DMII patients, as they are characterized by an increased oxidative stress status and changes will be larger if baseline concentrations are higher. Therefore, we would expect a change of 0.15 ng/mL in plasma 7b-OH-campesterol concentrations in DMII patients. Using this true change of 0.15 ng/mL and the known within-subject variation on the response of 0.14 ng/mL, it can be calculated that we need 18 subjects to have a power of 80% to detect the indicated difference, if we consider a P-value < 0.017 (to account for multiple comparisons between

groups) to be statistically significant. The expected dropout rate is 10%. Therefore, 20 diabetic patients will be recruited.

## 5. TREATMENT OF SUBJECTS

Subjects will be asked to consume three times daily (one at breakfast one at lunch and one at dinner) either control capsules, vitamin E capsules (900 mg) or lipoic acid capsules (600 mg) for three periods of four weeks. Each test period is separated by a washout period of 4 weeks, during which the subjects will return to their normal pattern (indicating no vitamin supplementation). During the entire study period (including the washout periods), the subjects are not allowed to consume any dietary supplements other than those provided by us. They will visit the department on 9 occasions (weeks 1, 3, 4, 9, 11, 12, 17, 19 and 20) to donate a blood sample, which is explained into more detail in §6.3.

### 5.1 Investigational products

Basic Pharma (Geleen, the Netherlands) will produce vitamin E, lipoic acid and matching placebo capsules to ensure the double-blind design. Production will be according to GMP and appropriate testing to ensure quality will be performed. The certificates of analysis are found in Appendix 3, the product specification files are found in Appendix 4 and the technical and quality assurance agreements with Basic Pharma are found in Appendix 5.

**Vitamin E:** Vitamine E capules will be administered orally, 1 capsule of 300mg, 3 times per day, equivalent to 900mg daily. Subjects will be advised to take the capsule after each meal with a glass of water.

**Lipoic acid:** Lipoic acid capules will be administered orally, 1 capsule of 200mg, 3 times per day, equivalent to 600mg daily. Subjects will be advised to take the capsule after each meal with a glass of water.

**Placebo:** Placebo capsules will be filled with gelatine, cellulosum microcristallinum PH102 and will also be administered orally 3 times per day using the same instructions as described for vitamin E and lipoic acid.

### 5.2 Product handling and storage

Vitamin E, lipoic acid and placebo capsules will be packed into separate boxes labelled with the number of capsules to be taken daily for a period of 1 week, the format for these labels is presented in appendix 2. One box will contain 23 capsules (which is 2 more than necessary) and labelled as box A, B or C. Labelling A, B and C is used to blind the capsules for investigator and subjects. Labelled boxes will be shipped to the Department of Human Biology, MUMC+. The boxes will be stored in the storage room (room 0.325a)

of the metabolic kitchen of the Metabolic Research Unit Maastricht (MRUM). They will be stored in a dry location, below 25 °C, protected from exposure to environmental changes. At the end of the study the boxes must be returned to the researchers to calculate (non)-compliance.

## 6. METHODS

### 6.1 Study parameters/endpoints

We will analyse parameters related to the research questions as described below. Based on new insights related to the original research question, it may be decided to analyse the samples for other parameters. Therefore, subjects will explicitly be asked in the informed consent form to consent (or not) with this approach.

#### 6.1.1 Metabolic risk markers

- Oxidative stress markers

Butylated hydroxy toluene (BHT) will be added to the EDTA blood collection tubes to prevent auto-oxidation of the sterols and other components in the blood.

The following oxidative stress markers will be determined in plasma:

- Plasma oxyphytosterol concentrations, measured in week 1, 4, 9, 12, 17 and 20
- Plasma oxysterol concentrations, measured in week 1, 4, 9, 12, 17 and 20
- Plasma oxidized LDL concentrations, measured in week 1, 4, 9, 12, 17 and 20
- TBARS assay, measured in week 1, 4, 9, 12, 17 and 20

- Antioxidant capacity

The following antioxidant concentration will be measured to determine compliance of the subjects and to determine antioxidant capacity:

- Plasma vitamin E concentrations, measured in week 1, 4, 9, 12, 17 and 20
- Plasma lipoic acid concentrations, measured in week 1, 4, 9, 12, 17 and 20
- Glutathion concentrations, measured in week 4, 12 and 20
- Plasma uric acid concentrations, measured in week 4, 12 and 20
- Trolox antioxidant capacity, measured in week 4, 12 and 20

- Lipid and lipoprotein concentrations

The following lipid and lipoprotein concentrations will be measured to assess determinants of the lipid metabolism:

- TCH concentrations, measured in week 1, 3, 4, 9, 11, 12, 17, 19 and 20
- HDL-C concentrations, measured in week 1, 3, 4, 9, 11, 12, 17, 19 and 20

- TAG concentrations, measured in week 1, 3, 4, 9, 11, 12, 17, 19 and 20
  - ApoB100 concentrations, measured in week 1, 3, 4, 9, 11, 12, 17, 19 and 20
  - ApoA-1 concentrations, measured in week 1, 3, 4, 9, 11, 12, 17, 19 and 20
- Glucose metabolism
    - Glucose concentrations, measured in week 4, 12 and 20
  - Low-grade inflammation and endothelial activity

The following parameters will be measured to assess concentrations of low-grade inflammation and endothelial activity:

- hsCRP, TNF- $\alpha$ , TNF-RI, TNFR-II, IL-6, MCP-1, sICAM-1, sVCAM-1 and sE-selectin, measured in week 4, 12 and 20
- Iron and copper status
- The following markers will be measured to assess iron and copper status. Iron and copper are the main metals present in human sera, and an increased metal status could indicate a higher oxidative susceptibility.
- Total iron, measured in week 4, 12 and 20
  - Transferrine, measured in week 4, 12 and 20
  - Ferritine, measured in week 4, 12 and 20
  - Copper, measured in week 4, 12 and 20
  - Ceruloplasmin, measured in week 4, 12 and 20

### 6.1.2 Food intake

Habitual food intake will be measured at the end of each test period using a validated food frequency questionnaire, which will be checked in the presence of a dietician immediately.

### 6.1.3 Body weight

Body weight without shoes and heavy clothing will be measured during each visit to the department.

## 6.2 Randomisation, blinding and treatment allocation

The subjects will receive the three experimental periods in a randomized order, based upon a computer-generated table with random numbers. For this, a categorical list in logical order will be created including all interventions per subject. After addition of a

computer-generated list of random numbers, the list will be sorted by subject number and random number, resulting in a randomized list of treatment allocation. The randomization code will be broken after statistical analyses are completed. For randomization, subjects will be stratified for gender. To blind the researchers and the subjects, the capsules will be packed and coded by Basic Pharma, an independent company.

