**APPENDIX 1: Study design**

Table 1. Study design

|                   | Period I             |   |   |   | Wash-out period | Period II            |    |    |    | Wash-out period | Period III           |    |    |    |
|-------------------|----------------------|---|---|---|-----------------|----------------------|----|----|----|-----------------|----------------------|----|----|----|
| Order I           | Control capsules     |   |   |   |                 | Vitamin E capsules   |    |    |    |                 | Lipoic acid capsules |    |    |    |
| Order II          | Control capsules     |   |   |   |                 | Lipoic acid capsules |    |    |    |                 | Vitamin E capsules   |    |    |    |
| Order III         | Vitamin E capsules   |   |   |   |                 | Lipoic acid capsules |    |    |    |                 | Control capsules     |    |    |    |
| Order IV          | Vitamin E capsules   |   |   |   |                 | Control capsules     |    |    |    |                 | Lipoic acid capsules |    |    |    |
| Order V           | Lipoic acid capsules |   |   |   |                 | Control capsules     |    |    |    |                 | Vitamin E capsules   |    |    |    |
| Order VI          | Lipoic acid capsules |   |   |   |                 | Vitamin E capsules   |    |    |    |                 | Control capsules     |    |    |    |
| Week              | 1                    | 2 | 3 | 4 | 5-8             | 9                    | 10 | 11 | 12 | 13-16           | 17                   | 18 | 19 | 20 |
| Blood sampling    | x                    |   | x | x |                 | X                    |    | x  | x  |                 | x                    |    | x  | x  |
| Food intake       |                      |   |   | x |                 |                      |    |    | x  |                 |                      |    |    | x  |
| Body weight       | x                    |   | x | x |                 | X                    |    | x  | x  |                 | x                    |    | x  | x  |
| Picking up supply | x                    |   |   |   |                 | x                    |    |    |    |                 |                      | x  |    | x  |

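### The list-and-sort procedure in section 6.2 makes the stated gender stratification ineffective and leaves chance imbalance over the six treatment orders unlimited

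*Protocol*

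**What the plan says.** Section 6.2 of the protocol sets out one mechanism in three steps. First, "a categorical list in logical order will be created including all interventions per subject". Second, computer-generated random numbers are added. Third, "the list will be sorted by subject number and random number, resulting in a randomized list of treatment allocation". The section then adds: "For randomization, subjects will be stratified for gender". Gender is not a sort key, and no separate lists, blocks or quotas of orders per gender are described. An independent company packs and codes the capsules.

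Table 1 in Appendix 1 shows all six possible orders of control, vitamin E and lipoic acid. It gives no number of subjects per order, and no section says that the orders will be used equally often.

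Section 4.5 plans 18 evaluable and 20 recruited subjects. Section 6.5 says that withdrawn subjects are not replaced. Section 8.2 names an ANOVA of differences from control and mentions no period term.

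**The concern.** Stratification affects an allocation only when something, such as a block or a quota, ties subjects in the same stratum together. Here the first sort key is the subject number, so each subject's three rows stay together and the random number only shuffles treatments within that subject. No subject's order depends on another subject's order or on gender. The stratification sentence and the procedure therefore do not fit together: the procedure is simple randomisation over six orders, whatever the gender mix.

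At stake is the spread of treatments over periods in a small trial. If the orders come out uneven, treatment is partly aligned with period. When period is modelled, that costs precision. When it is not, a change over the 20 weeks leaks into the treatment contrast of the list that happened to be drawn. An analysis plan can add a period term later, but it cannot rebalance a list that has already been used.

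**Working it through.** **Inputs.** 20 recruited, 18 completers, difference 0.15 ng/mL, within-subject SD 0.14 ng/mL, alpha 0.017 (all section 4.5). Two-sided testing is assumed, because the protocol does not say. The six orders come from Table 1.

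**1. The plan's own figure.** Section 4.5 says "we need 18 subjects to have a power of 80% to detect the indicated difference". With 0.14 as the within-subject SD, a paired difference has SD 0.14 × √2, and n = 2 × [(2.387 + 0.842) × 0.14 / 0.15]² = 18.16. The stated 18 is reproduced by the normal approximation, and 10% dropout gives 18 / 0.90 = 20. The randomisation issue does not change this figure.

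**2. What the procedure produces.** Each subject gets one of six orders with probability 1/6, independently. The counts per order are Multinomial(20; 1/6 each). Running the same sort separately for men and women gives the same distribution.

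**3. Imbalance with 20 subjects.**
- Chance that at least one order is unused, by inclusion-exclusion, Σ(−1)^(k+1) C(6,k) ((6−k)/6)^20 = 0.152.
- Chance of the most even split (4,4,3,3,3,3): 15 × 20! / (4!² × 3!⁴) / 6²⁰ = 0.013.
- Chance that the largest and smallest orders differ by 4 or more (simulated): 74%.
- Control in period I is Binomial(20, 1/3), with mean 6.7, SD √(20 × 1/3 × 2/3) = 2.1 and 95% range 3 to 11.

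**4. Cost with period in the model, 18 completers.** With three subjects per order, the error df are 54 − 1 − 17 − 2 − 2 = 32, the noncentrality is 0.15 / (0.14 × √(2/18)) = 3.21 and the critical t is 2.52. Power is 75.3%. Over simulated simple allocations, the contrast variance is inflated by 6.6% on average (5.7% with 20 subjects), and mean power is 72.2%. The loss is about 3 points. The step from the planned 80% to 75.3% comes from using the t distribution and is not due to randomisation.

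**5. Shift without a period term, end-of-period values.** Assume a steady drift δ per period. The vitamin E minus control estimate then shifts by δ × the mean of (period of vitamin E − period of control). Over Orders I to VI this difference is +1, +2, −2, −1, +1, −1, with mean 0 and variance (1+4+4+1+1+1)/6 = 2. With 20 subjects the SD of the shift is δ × √(2/20) = 0.316 δ. The simulated 95th percentile of its absolute size is 0.60 δ. With blocks of six within gender and an assumed 10/10 split, the SD is 0.126 δ and the 95th percentile 0.25 δ. The protocol does not give δ, so as a range of assumptions:

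| δ (ng/mL) | 95th percentile, as written | 95th percentile, blocked |
|---|---|---|
| 0.02 | 0.012 | 0.005 |
| 0.05 | 0.030 | 0.0125 |
| 0.10 | 0.060 | 0.025 |

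**6. Does that shift damage the test?** 20,000 simulated trials per setting, paired t test, n = 20, no period term. At δ = 0.10, type I error is 0.019 as written and 0.006 blocked; power is 56% and 57%. At δ = 0.05, power is 71% and 72%.

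**7. What blocking guarantees.** Each complete block adds one to every order. The incomplete last block in each of the two lists adds 0 or 1. The gap between any two orders is therefore at most 2 at allocation, whatever the gender split. With a 10/10 split, control falls in period I for 5 to 8 subjects (95% range).

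**The case against.** The strongest reply is that independent permutation within each subject is legitimate randomisation and that the protocol never undertakes to balance the six orders. Both points are correct. A reader might infer from Table 1 that equal use of the orders was promised and then broken. The table lists the possible orders without counts and does not support that. The only internal conflict is with the gender sentence.

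A reader might also infer that failed stratification biases the comparison by gender. It does not: every subject is planned to take all three treatments, so gender cannot confound the within-subject contrast.

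A third tempting reading is that the trial faces a bias of 0.06 ng/mL, 40% of the 0.15 target. That rests on a drift of 0.10 ng/mL per period that the protocol does not give. It is a 95th percentile and not a typical value, and it averages to zero over allocations. Step 6 shows type I error near nominal and almost the same power under both schemes, so the power lost at that drift comes from leaving period out of the analysis. Section 8.2 is brief, and an analysis plan not shown may include period. Section 6.1.1 also schedules oxyphytosterols at the start and end of each period, and section 8.1 allows change from baseline. If such changes were analysed, a steady drift would cancel.

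What stands is that the stratification statement is not met by the stated mechanism, and that avoidable imbalance costs a little precision.

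**Conclusion.** The point holds in a limited form. As written, section 6.2 is simple randomisation over six orders, and its gender stratification has no effect. This follows from the sort rule alone and needs no assumption. The demonstrated cost is about 3 points of power (72% against 75%), given a period term, 18 completers and the section 4.5 inputs with two-sided testing. A shift of the estimate in the realised list is possible if end-of-period values are analysed without period. It scales with a drift of unknown size, and the blocked comparison assumes 10 men and 10 women. Validity and average unbiasedness are not in question. Severity is minor to moderate. The reason to act is that the repair is nearly free and cannot be made after allocation.

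**What to change.** Before the first subject is allocated, replace the sorting procedure in section 6.2. Allocate subjects to the six orders of Table 1 in permuted blocks of six, each block containing every order once, with one list for men and one for women. The independent packer prepares and holds both lists. The stratification sentence then becomes true.

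The cost is one regenerated list and a short rewrite, with no added subjects or visits. Some imbalance remains from the incomplete last block in each list and from dropouts, who are not replaced. If one gender is rare, its list may never complete a block, but the overall gap of at most 2 at allocation still holds. Blocking does not replace a period term: without one, step 6 shows that under strong drift the blocked test becomes conservative. The analysis should therefore include period as well.
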